**Figure 1 F1:**
[figure not shown]
**Flow diagram of inclusion, randomisation and allocated intervention received among 258 general practices assessed for eligibility, the former county of Aarhus, DK, 2009**. * People identified by an algorithm based on health registers 2008-2009, and associated with the practices in January 2011.

1) that more than 50% of the people with type 2 diabetes, who had participated in a diabetes-consultation during the past year from the project invitation-date, had attended a consultation with a nurse at least once (confirmed by the practice). A diabetes-consultation was defined as a consultation including examinations, such as blood tests and blood pressure measurement as well as a conversation about living with type 2 diabetes or treatment modalities, according to the three-month consultations in the National guidelines regarding type 2 diabetes care [11],

2) enrolment to the project before registration deadline (three weeks following the date of invitation).

To avoid contamination of the intervention to control-practices, practice registration numbers with the same addresses were defined as one practice. Thus, 40 practices were randomised into two groups, and allocated in a way that the distributions of associated patients were approximately the same in the two groups. Randomisation was performed by a statistician who was blinded to the identity of the practices.

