#### Implementation of the course content in daily practice

Between the course afternoons, we encouraged the participating nurses to fill in worksheets specifically designed for the nurses' own potential changing process. These worksheets were counterpart to the patient-worksheets, but contended issues regarding implementation of the course content in daily practice. On course day 3, we encouraged the nurses to enact a consultation with a person with type 2 diabetes from their own practice.

On course day 3 and 4, half of the time was spent on exchanging experiences from implementing the course content in daily practice, perceived barriers, and feasible actions.

The aim of the ten month-visit in the practice from one of the course-teachers was to discuss the application of the course content in daily practice.

Changed behaviour with regard to autonomy support was self-rated by the nurses 11 months after the core intervention by a mailed questionnaire.

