### Statistical analyses

The primary analyses will be based on the intention-to-treat principle. As baseline value, the average value of the values measured within the last 12 months before course start will be used. The follow up-value will be the average value of the values measured during the 6 months following 15 months after the core intervention. Effectiveness of the intervention on HbA1c and cholesterol levels will be estimated by the differences between the diabetes populations in the intervention practices and the control practices with regard to 1) mean follow up-HbA1c and cholesterol, and 2) proportions with HbA1c≥8%, and proportions with Total cholesterol ≥5 mmol/l. The differences will be adjusted for baseline values. Differences in the proportions of the diabetes populations with measurements performed will also be assessed. Effectiveness of the intervention on score for PAID, SF-12(mental health), HCCQ, TSRQ and PCSD will be assessed by the difference between the diabetes populations in the intervention practices compared to the control practices 16 months after the core intervention.

Differences in the primary outcomes will be adjusted for age, gender, ethnicity, educational-level, and redeemed diabetes medication in the baseline-period. The analyses will be based on mixed models with including practice as a random factor in order to adjust for correlation within practices. Per-protocol analyses, including practices confirming changed behaviour and people with diabetes confirming participation in a nurse-led diabetes consultation, will be performed. Furthermore, subgroup analyses will be performed with regard to age, gender, and educational-level.

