## Discussion

This paper described an intervention aiming to improve autonomy support for people with type 2 diabetes in general practice, and the methods of evaluating the impact.

Jolly K, el al. [30] and Williams G, C et al. [15] also described the training of professionals in order to achieve autonomy supportive skills. These training programmes also included communication training, updated knowledge about treatment guidelines, focus on interactive learning, and implementation.

In our study, the intervention was offering the training course in a real-world setting. The recruitment strategy was a realistic scenario for future training courses. The design of our study was highly pragmatic [31] as there was no run-in period for the participating nurses, and according to the inclusion of an unselected diabetes population. It was possible to identify an unselected diabetes population owing to the availability of the Danish registers. A limitation is the database's inability to distinguish between types of diabetes, but the number of type 2 diabetes far exceeds the type 1 cases, and the ratio between the types will be equal distributed between the intervention - and the control group. The inclusion of the type 1 population may however, dilute the potential effect of the intervention because type 1 diabetes care is primarily delivered by out-patient clinics. The pragmatic design is challenging with respect to demonstrating the impact of the intervention. Not all the intervention practices participated in all or even in parts of the course. In the study of Williams G, C et al. [15], the health care providers were trained until the intervention could be delivered effectively. The participating practice nurses in our study might not have changed their behaviours, and the study population might not have participated in a diabetes consultation and/or changed behaviour during the time-period. HbA1c- and cholesterol measurements have the ability to change within a short time-period given changed behaviour, but the method and interval to the behaviour change vary. The decision regarding a sufficient follow-up time is therefore challenging. The SDT-based outcomes' ability to measure change is less investigated. Another challenge of demonstrating the impact of the intervention is that an allocation to a control group may have tempted the nurses in the control practices to join another training course.

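### The secondary per-protocol analysis selects practices on nurses' self-reported change, an effect of the course, rather than on having received the course

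*Protocol article*

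**What the plan says.** Under Statistical analyses, the protocol article bases the primary analyses on intention to treat and then adds: "Per-protocol analyses, including practices confirming changed behaviour". The same sentence also filters individual people, by whether they report a nurse-led consultation. This point concerns the practice filter only.

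The section does not define confirmation of changed behaviour. The one measurement described, in the section Implementation of the course content in daily practice, is the following: "Changed behaviour with regard to autonomy support was self-rated by the nurses 11 months after the core intervention by a mailed questionnaire". Linking the two is an inference, but the article offers no other source.

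The Discussion bears on the point in four places:
- It defines what was randomised: "In our study, the intervention was offering the training course in a real-world setting".
- It reports incomplete uptake: "Not all the intervention practices participated in all or even in parts of the course".
- It treats change as a separate matter from uptake: "The participating practice nurses in our study might not have changed their behaviours".
- It names a way in which control nurses could change without this course: "an allocation to a control group may have tempted the nurses in the control practices to join another training course".

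The legend of Figure 1 describes a "Flow diagram of inclusion, randomisation and allocated intervention received among 258 general practices", so receipt of the intervention appears to have been tracked. The figure itself is not shown.

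**The concern.** A per-protocol set is normally meant to keep the units that received what they were allocated. Here, a practice whose nurses attended every session but reported no change is excluded, although it received the intervention in full. The rule therefore removes treatment failures rather than non-adherence. It also relies on a rating by nurses who know whether they took the course, and only nurses who return the questionnaire can confirm anything.

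The article warns that its pragmatic design makes an impact hard to demonstrate and gives incomplete participation as one reason. If the intention-to-treat result is null, the per-protocol result is where one would look for the effect of actually receiving the course. A set chosen on reported success cannot supply that. It could show a benefit from a course that does nothing.

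**Working it through.** **Step 1. What the rule selects under each reading.** The article does not say how the filter applies to control practices.

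| Reading | Intervention practices kept | Control practices kept | What is compared |
|---|---|---|---|
| Intervention arm only | those reporting change | all | self-declared successes with an unselected group |
| Both arms | those reporting change | those that changed without this course | two selected groups, with unchanged controls removed |

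The first is the more natural reading, because the self-rating is described within the account of the intervention. Neither row estimates the effect of receiving the course.

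**Step 2. Size under the first reading, with no true effect.** The plan has no figure of its own to reproduce. From the document: 40 practices in two groups. Assumed: 20 per arm, 60 people per practice, ICC 0.02 to 0.05, the best-rated 50 to 70% of intervention practices retained, and correlation *r* of 0.3 to 0.5 between self-rating and the practice's underlying level. No baseline adjustment.

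The expected spurious difference in SD units is about *r* × √ICC × *i*, where *i* is the mean of a standard normal variable above the cut-off for the retained share: 0.798 for the top 50% and 0.497 for the top 70%.

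- ICC 0.02 (√ICC = 0.141), smallest: 0.3 × 0.141 × 0.497 = 0.021. Largest: 0.5 × 0.141 × 0.798 = 0.056.
- ICC 0.05 (√ICC = 0.224), smallest: 0.3 × 0.224 × 0.497 = 0.033. Largest: 0.5 × 0.224 × 0.798 = 0.089.

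Simulation (4000 replicates per setting, t-test on practice means) agrees. The simulated bias is slightly lower because the choice is made among only 20 practices.

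| ICC | Spurious difference (SD) | Two-sided false-positive rate |
|---|---|---|
| 0.02 | 0.022 to 0.054 | 6.5 to 10.8% |
| 0.05 | 0.032 to 0.085 | 6.4 to 13.4% |

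**Step 3. Sensitivity to *r*.** At *r* = 0 the formula gives zero, and the simulated false-positive rate is about 5%. At *r* = −0.3 the sign reverses, to about −0.02 to −0.05 SD.

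**Step 4. Baseline adjustment.** The plan adjusts HbA1c and cholesterol for baseline values. Assuming baseline-to-follow-up correlations of 0.8 between practices and 0.6 between patients, the bias falls to about 0.01 to 0.03 SD and the false-positive rate to about 5 to 8%. The questionnaire outcomes (PAID, SF-12 mental health, HCCQ, TSRQ, PCD) are compared at 16 months with no baseline score described, so Step 2 applies to them.

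**Step 5. Both readings side by side.** A separate null simulation used HbA1c with about 101 people per practice (4034/40), assumed SD 1.25, ICC 0.02 to 0.10, and no baseline adjustment. About half of intervention practices and 20 to 30% of control practices were assumed to confirm change. The log-odds of confirming rose by 0.5 to 2 per SD of practice quality.

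- Intervention arm filtered: −0.04 to −0.24 HbA1c points, a false benefit.
- Both arms filtered: +0.03 to +0.11 points, the opposite direction. Replicates with fewer than three practices left in an arm were discarded.

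These values are useful for direction only. They omit the planned baseline adjustment and so overstate the size for HbA1c.

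**The case against.** The strongest reply is that this is one sentence about an added analysis. The primary analysis is intention to treat, which matches an intervention defined as the offer of a course, and no primary conclusion depends on the per-protocol set. That stands.

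A second reply is that the criterion measures fidelity. The Discussion lists links that may fail (attendance, change in nurses, patients' contact with a nurse), and the two filters match the last two. As a motive this is reasonable. It does not make the groups comparable, because enactment is self-reported after randomisation and has no clean counterpart among controls.

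A third reply is that the figures rest on assumptions. This stands too. The document gives no correlation. A negative one is plausible, since a practice starting low has more room to report change.

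A reader might infer three stronger things that the document does not support:
- **That the result is inflated by a known amount, or certainly inflated.** Neither the size nor the sign is fixed by anything in the article.
- **That 6 to 13% describes HbA1c and cholesterol.** It leaves out their planned baseline adjustment.
- **That session-by-session attendance records exist and are being ignored.** The article shows that non-participation was known, and the Figure 1 legend refers to receipt. It describes no attendance register.

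**Conclusion.** The point holds as a defect in a stated secondary analysis. The practice-level rule conditions on a self-reported effect of the course, and neither way of handling controls recovers the effect of receiving it. This conclusion comes from the text and needs no number. It does assume that the confirmation meant is the nurses' 11-month self-rating.

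The size is illustrative: about 0.02 to 0.09 SD and a false-positive rate of about 6 to 13% for the questionnaire outcomes. That assumes filtering of the intervention arm only, a correlation of 0.3 to 0.5, ICC 0.02 to 0.05 and 50 to 70% of practices retained. It is smaller for HbA1c and cholesterol, absent at zero correlation, and reversed if the correlation is negative. The change should be made, but the main result of the trial does not depend on it.

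**What to change.** Remove confirmation of changed behaviour as the practice-level inclusion rule. In its place, estimate a complier-average effect with randomised arm as instrument, keeping all 40 practices, the same covariates and the practice random effect.

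Define receipt as any participation in the course. The method assumes that the offer does nothing in practices coded as not receiving it. That is plausible for practices that took no part. It is doubtful if partial attenders are coded as non-receivers, and the article says some practices missed parts of the course. Completion of the two core afternoons, or number of sessions, should therefore be a sensitivity analysis only, where records allow, with the stronger assumption stated.

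Report nurses' self-rated change as a descriptive process measure.

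The cost is a change of wording and one further model, using participation data that appear to be held. The interval widens, because the estimate and its standard error both scale by about 1/attendance share. With an assumed share of 0.7, that is 1/0.7 = 1.43. Since both scale together, there is no gain in power over intention to treat.

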### Sample size and power

It was estimated that with a minimum of 30 practices, a difference on 0.5% in mean HbA1c could be detected with a power on 90% under the assumption that 50% of the diabetes population participated in a nurse-consultation.

### Ethical approval

The study will be conducted according to the Helsinki Declaration. The Danish Research Ethics Committee assessed the trial not to be a biomedical intervention, and because the intervention was addressed the nurses, informed content of the diabetes population should not be obtained. The study was approved by the Danish Data Protection Agency (j.no: 2009-41-3065), and it was registered at ClinicalTrials.gov (Identifier NCT01187069).

## Discussion

This paper described an intervention aiming to improve autonomy support for people with type 2 diabetes in general practice, and the methods of evaluating the impact.

Jolly K, el al. [30] and Williams G, C et al. [15] also described the training of professionals in order to achieve autonomy supportive skills. These training programmes also included communication training, updated knowledge about treatment guidelines, focus on interactive learning, and implementation.

In our study, the intervention was offering the training course in a real-world setting. The recruitment strategy was a realistic scenario for future training courses. The design of our study was highly pragmatic [31] as there was no run-in period for the participating nurses, and according to the inclusion of an unselected diabetes population. It was possible to identify an unselected diabetes population owing to the availability of the Danish registers. A limitation is the database's inability to distinguish between types of diabetes, but the number of type 2 diabetes far exceeds the type 1 cases, and the ratio between the types will be equal distributed between the intervention - and the control group. The inclusion of the type 1 population may however, dilute the potential effect of the intervention because type 1 diabetes care is primarily delivered by out-patient clinics. The pragmatic design is challenging with respect to demonstrating the impact of the intervention. Not all the intervention practices participated in all or even in parts of the course. In the study of Williams G, C et al. [15], the health care providers were trained until the intervention could be delivered effectively. The participating practice nurses in our study might not have changed their behaviours, and the study population might not have participated in a diabetes consultation and/or changed behaviour during the time-period. HbA1c- and cholesterol measurements have the ability to change within a short time-period given changed behaviour, but the method and interval to the behaviour change vary. The decision regarding a sufficient follow-up time is therefore challenging. The SDT-based outcomes' ability to measure change is less investigated. Another challenge of demonstrating the impact of the intervention is that an allocation to a control group may have tempted the nurses in the control practices to join another training course.

The advantages of our study design are 1) the random distribution of practice characteristics in the intervention - and the control group minimising potential confounding, and 2) the high applicability of the results to real-world practice because of the high pragmatics of attitude in our study. In a real-world setting, this study will determine the impact on the motivation, HbA1c, cholesterol, and well-being of people with diabetes by offering a training course for practice-nurses in general practices, where nurses provide diabetes consultations.
